##### Risky sex

Risky sex (e.g., number of partners, use of condoms) in the past month will be assessed with the Sexual Risk Survey (SRS), a 23-item measure designed and validated with college student samples [82]. The SRS will be modified to assess past month behavior as opposed to past 6-month behavior so we can assess this outcome during equal time periods across surveys. The SRS allows for open-ended responses that are then recoded into ordinal categories for generating an overall score, as well as five composite scores of sexual risk taking with uncommitted partners, risky sex acts, impulsive sexual behaviors, intent to engage in risky sexual behavior, and risky anal sex acts [83]. A composite SRS score will be used in analyses as the risky sex outcome, with specific subscale scores examined descriptively.

##### Sexual violence victimization

Sexual violence victimization will be assessed primarily with the Sexual Experiences Survey (SES) [84–86], validated with college students and used in prior work with study abroad students [16, 17, 25]. The measure will be modified and informed by items from the National Drug-Facilitated, Incapacitated, and Forcible Rape study [87] to include 12 gender- and sex-specific items that reflect five aspects of sexual violence victimization: non-consensual/unwanted sexual contact, sexual coercion, completed sexual assault by force, alcohol- and drug-facilitated sexual assaults, and attempted sexual assault, as well as a composite score of any type of sexual violence victimization. The specific items and gender- and sex-specific wording are included in the Appendix. Response options at predeparture capture whether any sexual violence victimization was experienced prior to going abroad (both in college and prior to college). Participants will fill out the measure again during the last month abroad survey to reflect experience of any sexual violence victimization during the entire trip abroad. Finally, participants will complete the measure again during the 3-month post-return surveys to reflect whether they have experienced any sexual violence victimization since returning to the US from study abroad. Experience of any sexual violence abroad will be the main outcome for sexual violence victimization, but we will decribe the categories of non-consensual/unwanted sexual contact, sexual coercion, completed sexual assault by force, alcohol- and drug-facilitated sexual assaults, and attempted sexual assault descriptively.

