Participants will complete a survey approximately 2 weeks prior to departure, one survey during their first month abroad, one during their last month abroad, one during their first month back in the US, and a final follow up 3 months post-return to the US. The last survey completed abroad represents the final 30 days of the trip, which, for the majority of students in the study, will be the third month abroad. Length of program will be controlled for in analyses. Participants will receive a $20 Amazon gift card for each of these 15 to 20 min surveys that they complete. Email, text, and phone call reminders will assist with reducing attrition on surveys, which helped us retain 80% of participants in our pilot work and other RCTs [52, 76]. A diagram of participant flow through the intervention study is found in Fig. 1. Figure 2 contains a SPIRIT (Standard Protocol Items: Recommendations for Interventional Trials) flow diagram of the RCT schedule of enrollment, interventions, and assessments.

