*Response options at predeparture*: Regardless of how long ago it happened or who made the unwanted sexual advances…

- 0 = No, this has never happened to me
- 1 = Yes, this happened to me before I started college
- 2 = Yes, this happened to me during college
- 3 = Yes, this happened to me before college and during college

*Response options at last month abroad*: Consider your entire trip abroad. Regardless of when it happened during your trip or who made the unwanted sexual advances…

- 0 = No
- 1 = Yes

Also, on the last month abroad survey, all items will be prefaced with “During your study abroad trip…”

*Response options at 3-month post-return*: Consider the past 3 months (i.e., the time since you have been back in the US since your study abroad trip ended). Regardless of when during this time it happened or who made the unwanted sexual advances…

- 0 = No, this has not happened to me
- 1 = Yes, this happened to me since I have returned from study abroad

Also, on the 3-month post-return survey, all items will be prefaced with “During the past 3 months since you have been home from your study abroad trip…”

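### Sexual violence abroad is asked once, before the trip ends, and the next questionnaire starts at return, so the outcome covers the trip only up to the survey date.

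*Protocol article*

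**What the plan says.** Prevention of sexual violence victimisation abroad is one of the primary outcomes (Outcome measures), and any such experience abroad is the main sexual violence variable (Sexual violence victimization). That section gives the measure three times.

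- **Predeparture:** lifetime history.
- **Last month abroad:** "during the last month abroad survey to reflect experience of any sexual violence victimization during the entire trip abroad". The Appendix wording is "Consider your entire trip abroad. Regardless of when it happened during your trip", with a yes/no answer.
- **3 months post-return:** "participants will complete the measure again during the 3-month post-return surveys to reflect whether they have experienced any sexual violence victimization since returning". The Appendix defines the period as "the time since you have been back in the US since your study abroad trip ended", and the only positive answer refers to events since return.

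The 1-month post-return survey is not listed for this measure. On timing, Procedures schedules "one survey during their first month abroad, one during their last month abroad" and adds: "The last survey completed abroad represents the final 30 days of the trip". No day or window within that last month is given. Eligible trips last 8 to 20 weeks (Participants).

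**The concern.** A question about the entire trip can cover it only if it is asked once the trip is over. Here the student answers while some of the trip is still to come, and the next questionnaire begins at return. The days in between belong to no recall period. A student with no earlier event abroad who is victimised in those days is scored as having none.

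Three things are at stake. The variable does not measure what its definition says. The share of the trip observed differs between students according to when they answer and how long they stay. Events, and with them some power, are lost on an outcome that the protocol treats as primary.

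The past-month drinking and risky-sex measures differ in this respect: their recall period has the same length whenever they are answered. Only the sexual violence measure claims the whole trip.

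**Working it through.** **1. Recall windows side by side**

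| Administration | Window starts | Window ends |
|---|---|---|
| Last month abroad | departure | date the survey is answered |
| 3 months post-return | return to the US | date of that survey |

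The interval from the date answered to the date of return appears in neither row. Call its length g days. It can run from 0 (answered on the last day) to about 30 (answered at the start of the last month).

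**2. Share of the trip unobserved**

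Share = g / T, with T the trip length in days. The 8 and 20 weeks come from Participants, giving T = 56 and 140. Procedures says that for most students the final 30 days will be the third month, so 13 weeks (T = 91) serves as a middle case. The values of g are assumptions.

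| g | 8 weeks | 13 weeks | 20 weeks |
|---|---|---|---|
| 7 days | 7/56 = 12.5% | 7/91 = 7.7% | 7/140 = 5.0% |
| 15 days | 15/56 = 26.8% | 15/91 = 16.5% | 15/140 = 10.7% |

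**3. What this does to the comparison**

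The article states that 1200 students suffice for small to moderate effects but gives no event rate, effect value, alpha or power, so there is no figure of its own to reproduce. The following is an illustration under these assumptions:

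- whole-trip control risk P = 20% and risk ratio 0.70, so 14% with intervention;
- constant hazard over the trip;
- the same g in both arms;
- two-sided alpha 0.05;
- 480 per arm (600 × 0.80, using the 80% retention cited in Procedures).

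Observed risk = 1 − (1 − P)^(1 − g/T). For a 13-week trip and g = 7, the exponent is 1 − 7/91 = 0.923:

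- control: 1 − 0.80^0.923 = 18.6%
- intervention: 1 − 0.86^0.923 = 13.0%

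| 13-week trip | Control | Intervention | Difference | Risk ratio | Power |
|---|---|---|---|---|---|
| no gap | 20.0% | 14.0% | 6.0 points | 0.700 | 0.697 |
| g = 7 | 18.6% | 13.0% | 5.6 points | 0.698 | 0.665 |
| g = 15 | 17.0% | 11.8% | 5.2 points | 0.696 | 0.625 |

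Power is for a simple comparison of two proportions, without the school-level clustering.

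With P varied from 10% to 40% at the same risk ratio, g = 7 costs about 1 to 3 points of power on a 13-week trip and about 1 to 5 points on an 8-week trip. For g = 15 on a 13-week trip the cost is about 2 to 7 points.

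**The case against.** The strongest reply is the statement in Procedures that the survey represents the final 30 days of the trip. A past-month survey can do that only if it is answered close to the end, so the intended gap is short. The exact survey window is operational detail that an article may leave to the full protocol, and the SPIRIT schedule (Fig. 2) is not shown. This stands as to size. It does not close the gap: the article otherwise asks only for "one during their last month abroad", and any day between answering and return is still outside both windows.

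Three further points also limit the weight of the concern.

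- The outcome is any event abroad. A student who already reported one is counted, so only first events in the gap are lost, and the share of time overstates the share of outcome lost.
- Both arms follow the same schedule. Unless completion timing differs by arm, or the effect changes late in the trip, the under-count is non-differential.
- Programme length will be adjusted for in analyses. That partly handles differences in trip length but recovers no events, and it does not capture the completion date.

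A reader might infer more than the documents support. One inference is that up to 54% of a short trip is missed (30/56). That needs a survey answered 30 days before the end, which conflicts with its stated purpose. Another is that about 20% of students will lack this outcome. The 80% retention is a general figure from the pilot and other trials (80% or better in the Discussion), not the non-response at this wave, and the handling of missing data may be set out in an analysis plan that is not shown. A third is that the treatment comparison is biased. Nothing in the article points to different timing by arm.

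**Conclusion.** The gap is real and follows from the printed recall wording: as measured, the outcome is victimisation from departure to the survey date, not over the entire trip. Its length is unknown because the survey day is not fixed. At about 7 days it leaves 5% to 12.5% of trip time unobserved, depending on programme length; earlier completion leaves more. With similar timing in both arms the event rate and absolute difference fall, power falls by a few points under the assumed rates, and the risk ratio hardly changes. The shares of trip time rest only on trip length and the assumed gap. The effects on risk and power also rest on the assumed event rate, risk ratio, constant hazard and equal timing by arm. The point is worth correcting because the outcome is primary and the correction is cheap; it does not threaten the validity of the comparison.

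**What to change.** Keep the items on the last survey abroad. Add the same items to the existing 1-month post-return survey, prefaced with wording such as 'since your last survey while still abroad'; for students who missed that survey, ask about the whole trip. Score any victimisation abroad as positive if reported on either survey, and leave the 3-month version as it is. The trip and post-return windows then meet, and some students who missed the last survey abroad gain a value.

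The cost is up to 12 more sensitive items on one survey and slightly longer recall for the final days abroad. Moving all the trip items to the 1-month survey would also close the gap, but it lengthens recall for the whole trip and makes a primary outcome depend entirely on a later wave, so the bridging question is preferable.

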### Mediator and moderator effects on the intervention

We will investigate the mechanisms of effects through mediation (changes in perceived norms; experience with sojourner adjustment). Mediation will be investigated within the multilevel modeling framework, using bootstrapping to investigate the standard errors (and hence statistical significance) of mediated effects [88–91]. Second, we will investigate potential moderators (age, gender, host country, institution type, race/ethnicity, baseline drinking, drinking motives while abroad, predeparture expectancies, history of sexual violence) of the association between the intervention and main outcomes by incorporating multiplicative interaction terms into the model described above. Given the high number of candidate moderators in our analyses, we will adjust for multiple testing concerns in our moderation analyses by using a Benjamini–Hochberg adjustment to the *p*-value.

#### Measures of mediators

The intervention has two major components (PNF and SAF), and we have included measures to assess whether changes in perceptions and engagement in positive sojourner adjustment mediate observed effects of the intervention.

##### Perceptions

Using a modified Drinking Norms Rating Form (DNRF) [92] participants will be asked about perceived drinking of a typical gender-specific study abroad student in their host country and of a typical native in their host country (i.e. someone born in the country and living there currently). The DNRF is modeled after the DDQ to assess perceptions for each reference group regarding perceived total drinks per week, perceived drinking days, and perceived average drinks during a typical month during the same time period the participants is studying abroad. Perceived number of heavy drinking days per month will also be assessed. Changes in these perceptions (average drinks per occasion, heavy drinking days) are hypothesized to serve as mediators of the intervention as these two perceptions will be directly targeted in the PNF.

##### Sojourner adjustment

We will use the 24-item Sojourner Adjustment Measure (SAM; [77]) to assess the four positive and two negative sojourner adjustment factors. This scale contains a 7-point Likert scale (1 = disagree strongly to 7 = agree strongly) to assess engagement in the four factors of positive sojourner adjustment and two negative sojourner adjustment factors. The SAM will assess actual experience of the six factors abroad to examine changes in sojourner adjustment over time as a mediator of intervention effects. Each of the six factors will be included separately in analyses: the four positive factors of social interaction with host nationals, cultural understanding and participation, language development and use, host culture identification; the two negative factors of social interaction with co-nationals and homesickness/feeling out of place. The SAM factors have demonstrated adequate reliability and convergent validity with established measures of acculturation [77].

#### Measures of moderators

Based on prior work and pilot study findings, we hypothesize that younger students (i.e., those under age 21), men, those studying in Europe, those who drink for social and coping reasons abroad, those with expectancies that alcohol will play a large role in their experience while abroad, and baseline heavier drinkers will benefit most from the PNF + SAF intervention [9, 11, 52, 72]. Items on the predeparture survey will assess age, gender, and location of study. Drinking motives will be assessed in the two abroad assessments with two subscales from the 20-item Drinking Motives Questionnaire–Revised [93] regarding coping and social motives (5 items each). This measure has displayed adequate reliability in general student and study abroad student samples [10, 94, 95]. Expectancies about the role alcohol will play in the study abroad experience will be assessed at predeparture with a measure we have used in our study abroad work (α = 0.84 in prior work) [9]. Participants will rate their agreement with 13 statements (e.g., “I will drink alcohol more often abroad than I drink now,” “alcohol will make my study abroad experience more fun”) from 0 (strongly disagree) to 4 (strongly agree). Baseline heavy drinking will be defined as a continuous value for total drinks per week from the DDQ. History of sexual violence will be defined as any experience of sexual violence prior to abroad (either in college or prior to college). Institution type (small college/university vs large university) and student race/ethnicity will also be accessed and be examined as additional exploratory moderators.

## Discussion

### Limitations and alternative methods considered

We have considered alternative methodological approaches and attempted to address limitations to this study protocol. First, the use of longitudinal self-report measures collected via the Internet could be associated with attrition and bias. However, research suggests confidential surveys enhance reliability and that validity and response rates are higher for web than mailed surveys [96–99]. In addition, we achieved retention rates of 80% or better in the pilot study with multiple assessments while abroad [52].

Second, we considered potential iatrogenic effects from the PNF, but note that studies with college students have suggested that iatrogenic effects are rare in PNF interventions [40, 41]. Light drinkers and non-drinkers who receive PNF report less drinking and more sustained abstinence compared to non-PNF control participants [100]. The manner in which we frame our norms presentation also minimizes iatrogenic effects. For example, it may be accurate to state “only 1 in 10 students studying in Ireland abstained during their trip,” yet this message conveys that abstaining is actually atypical and *only* a few students do it. Instead, we would combine this information with moderate drinkers and frame the message as “80% of students studying in Ireland report drinking less than 3 drinks on a typical night,” which conveys that moderate drinking is typical. This is how we framed normative drinking messages in our pilot work [52].

Third, we chose three primary drinking outcomes because it allows us to see nuanced heavy and problematic behavior. Frequency may increase as a function of the culture abroad (e.g., wine with dinner) and may not be particularly problematic; thus heavy drinking in the form of total weekly quantity and frequency (total weekly drinks) and heavy drinking (i.e., drinking enough to be intoxicated; binge drinking), as well as number of consequences, are our outcomes of interest. We also focus on 12 locations to allow us to personalize the content. These common host countries are skewed European; however, these sites represent 60% of all students abroad [1] and we do include representation of the most popular Asian and Latin American host countries. If the approach is successful, country-specific content for the less popular sites abroad can be developed.

Lastly, we primarily focus on sexual assault victimization and not perpetration as we will likely be underpowered to report any meaningful effects on the low base rate of admitted perpetration in the sample. Both men and women report sexual risk abroad [9] and we include gender as a moderator in outcome analyses.

## Conclusion

In sum, the proposed RCT innovatively extends normative feedback interventions by examining a tailored PNF-adapted intervention that uses additional content regarding SAF to reduce alcohol and sexual risk in young adults studying abroad—a significant and understudied high-risk group entering into a risky foreign context. Although study abroad and student affairs personnel recognize drinking abroad and sexual risk as major concerns and desire empirically-based programs for students as they enter a known period of risk, there currently are few targeted resources for this population. If the proposed intervention is efficacious, as hypothesized, it can be widely implemented at institutions across the country to help prevent the problematic drinking behavior abroad that negatively affects students and institutions, as well as serve as a model to address alcohol risk for other young adults living and traveling abroad.

## Data Availability

Once collected, deidentified data from this study will be available by request to the corresponding author 1 year after all aims of the project are completed. Requestors of data will be asked to complete a data-sharing agreement that provides for (1) a commitment to using the data only for research purposes and not to identify any individual participant; (2) a commitment to securing the data using appropriate computer technology and (3) a commitment to destroying or returning the data after analyses are completed.

## Appendix

Modified sexual experiences survey reflecting study abroad context and incorporating items from the National Drug-facilitated, Incapacitated, and Forcible Rape Study

**Table Taba:**

Domain	Female item wording	Male item wording	Gender-neutral item wording
Introduction	Intro to items: Many women have experienced unwanted sexual advances at some point during their lives. Women do not always report such experiences to police or discuss them with family or friends. Such experiences can happen anytime in a woman’s life—even as a child. The person making these unwanted advances can be friends, boyfriends, girlfriends, coworkers, teaching assistants, supervisors, family members, strangers, or someone they just met. The person making the unwanted sexual advances can be male or female	Intro to items: Many men have experienced unwanted sexual advances at some point during their lives. Men do not always report such experiences to police or discuss them with family or friends. Such experiences can happen anytime in man’s life—even as a child. The person making these unwanted advances can be friends, girlfriends, boyfriends, coworkers, teaching assistants, supervisors, family members, strangers, or someone they just met. The person making the unwanted sexual advances can be male or female	Many people have experienced unwanted sexual advances at some point during their lives. Men and women do not always report such experiences to police or discuss them with family or friends. Such experiences can happen anytime in a person’s life—even as a child. The person making these unwanted advances can be friends, boyfriends, girlfriends, coworkers, teaching assistants, supervisors, family members, strangers, or someone they just met. The person making the unwanted sexual advances can be male or female
Nonconsensual/unwanted sexual contact (1 item)	1. Has anyone ever fondled, kissed, or rubbed up against the private areas of your body (lips, breast/chest, crotch or butt) or removed some of your clothes without your consent *(but did not attempt sexual penetration)*?	1. Has anyone ever fondled, kissed, or rubbed up against the private areas of your body (lips, chest, crotch or butt) or removed some of your clothes without your consent *(but did not attempt sexual penetration)*?	1. Has anyone ever fondled, kissed, or rubbed up against the private areas of your body (lips, breast/chest, crotch or butt) or removed some of your clothes without your consent *(but did not attempt sexual penetration)*?
Sexual coercion (2 items)	2. Has anyone ever had sex with you without your consent by telling lies, threatening to end the relationship, threatening to spread rumors about you, making promises you knew were untrue, or continually verbally pressuring you after you said you didn’t want to. By having sex, we mean that a man or boy put his penis in your vagina, your anus, or your mouth 3. Has anyone ever had sex with you without your consent by showing displeasure, criticizing your sexuality or attractiveness, getting angry but not using physical force, after you said you didn’t want to. By having sex, we mean that a man or boy put his penis in your vagina, your anus, or your mouth	2. Has anyone ever had sex with you without your consent by telling lies, threatening to end the relationship, threatening to spread rumors about you, making promises you knew were untrue, or continually verbally pressuring you after you said you didn’t want to. By having sex, we mean that a man or boy put his penis in your anus or your mouth, someone made you put your penis in their vagina or anus, or someone made you put your mouth on their vagina or anus 3. Has anyone ever had sex with you without your consent by showing displeasure, criticizing your sexuality or attractiveness, getting angry but not using physical force, after you said you didn’t want to. By having sex, we mean that a man or boy put his penis in your anus or your mouth, someone made you put your penis in their vagina or anus, or someone made you put your mouth on their vagina or anus	2. Has anyone ever had sex with you without your consent by telling lies, threatening to end the relationship, threatening to spread rumors about you, making promises you knew were untrue, or continually verbally pressuring you after you said you didn’t want to. By having sex, we mean that a man or boy put his penis in your vagina, your anus, or your mouth; someone made you put your penis in their vagina, anus, or mouth; or someone made you put your mouth on their vagina or anus 3. Has anyone ever had sex with you without your consent by showing displeasure, criticizing your sexuality or attractiveness, getting angry but not using physical force, after you said you didn’t want to. By having sex, we mean that a man or boy put his penis in your vagina, your anus or your mouth; someone made you put your penis in their vagina, anus, or mouth, or someone made you put your mouth on their vagina or anus
Completed sexual assault by force (4 items)	4. Has a man or boy ever made you have sex by using force or threatening to harm you or someone close to you? Just so there is no mistake, by having sex, we mean putting a penis in your vagina 5. Has anyone, male or female, ever made you have oral sex by force or threatening to harm you? So there is no mistake, by oral sex, we mean that a man or boy put his penis in your mouth or someone penetrated your vagina or anus with their mouth or tongue 6. Has anyone ever made you have anal sex by force or threatening to harm you? By anal sex, we mean putting their penis in your anus or rectum 7. Has anyone ever put fingers or objects in your vagina or anus against your will by using force or threatening to harm you?	4. Has a woman or girl ever made you have vaginal sex by using force or threatening to harm you or someone close to you? Just so there is no mistake, by vaginal sex, we mean putting your penis in a vagina 5. Has anyone, male or female, ever made you have oral sex by force or threatening to harm you? So there is no mistake, by oral sex, we mean that a man or boy put his penis in your mouth, someone made you put your mouth or tongue in their vagina or anus, or someone penetrated your anus with their mouth or tongue 6. Has anyone ever made you have anal sex by force or threatening to harm you? By anal sex, we mean putting their penis in your anus or rectum or making you put your penis in their anus or rectum 7. Has anyone ever put fingers or objects in your anus against your will by using force or threatening to harm you?	4. Has anyone, male or female, ever made you have vaginal sex by using force or threatening to harm you or someone close to you? Just so there is no mistake, by vaginal sex, we mean putting a penis in a vagina 5. Has anyone, male or female, ever made you have oral sex by force or threatening to harm you? So there is no mistake, by oral sex, we mean that a man or boy put his penis in your mouth, someone made you put your mouth or tongue in their vagina or anus, or someone penetrated your vagina or anus with their mouth or tongue 6. Has anyone ever made you have anal sex by force or threatening to harm you? By anal sex, we mean putting their penis in your anus or rectum or making you put your penis in their anus or rectum 7. Has anyone ever put fingers or objects in your vagina or anus against your will by using force or threatening to harm you?
Alcohol- and drug- facilitated sexual assaults (2 items)	Intro to section. Some women have had sex when they didn’t want to because they were very high, intoxicated, or even passed out because of alcohol or drugs. We would like to ask you about these types of experiences you might have had. Again, we are interested in these experiences regardless of how long ago it happened, who did it, or whether or not it was reported to police 8. Has anyone ever had sex with you when you didn’t want to after you drank so much alcohol that you were very high, drunk, or passed out? By having sex, we mean that a man or boy put his penis in your vagina, your anus, or your mouth 9. Has anyone ever had sex with you when you didn’t want to after they gave you, or you had taken enough drugs to make you very high, intoxicated, or passed out? By having sex, we mean that a man or boy put his penis in your vagina, your anus, or your mouth	Intro to section: Some men have had sex when they didn’t want to because they were very high, intoxicated, or even passed out because of alcohol or drugs. We would like to ask you about these types of experiences you might have had. Again, we are interested in these experiences regardless of how long ago it happened, who did it, or whether or not it was reported to police 8. Has anyone ever had sex with you when you didn’t want to after you drank so much alcohol that you were very high, drunk, or passed out? By having sex, we mean that a man or boy put his penis in your anus or your mouth, someone made you put your penis in their vagina or anus, or someone made you put your mouth on their vagina or anus 9. Has anyone ever had sex with you when you didn’t want to after they gave you, or you had taken enough drugs to make you very high, intoxicated, or passed out? By having sex, we mean that a man or boy put his penis in your anus or your mouth, someone made you put your penis in their vagina or anus, or someone made you put your mouth on their vagina or anus	Intro to section: Some people have had sex when they didn’t want to because they were very high, intoxicated, or even passed out because of alcohol or drugs. We would like to ask you about these types of experiences you might have had. Again, we are interested in these experiences regardless of how long ago it happened, who did it, or whether or not it was reported to police 8. Has anyone ever had sex with you when you didn’t want to after you drank so much alcohol that you were very high, drunk, or passed out? By having sex, we mean that a man or boy put his penis in your vagina, your anus, or your mouth; someone made you put your penis in their vagina or anus, or someone made you put your mouth on their vagina or anus 9. Has anyone ever had sex with you when you didn’t want to after they gave you, or you had taken enough drugs to make you very high, intoxicated, or passed out? By having sex, we mean that a man or boy put his penis in your vagina, your anus, or your mouth; someone made you put your penis in their vagina or anus, or someone made you put your mouth on their vagina or anus
Attempted sexual assaults (3 items)	10. Has anyone ever *attempted* to have vaginal, oral, or anal sex with you when you did not want to or put fingers or objects in your vagina or anus against your will *but was not successful*? 11. When you had been very *high, drunk, or passed out from alcohol,* has anyone ever *attempted* to have vaginal, oral, or anal sex with you or tried to put fingers or objects in your vagina or anus against your will *but was not successful*? 12. When you had been very *high, intoxicated, or passed out from drugs,* has anyone ever *attempted* to have vaginal, oral, or anal sex with you or tried to put fingers or objects in your vagina or anus against your will but was not successful?	10. Has anyone ever *attempted* to have oral, vaginal, or anal sex with you when you did not want to or put fingers or objects in your anus against your will *but was not successful*? 11. When you had been very *high, drunk, or passed out from alcohol,* has anyone ever *attempted* to have oral, vaginal, or anal sex with you or tried to put fingers or objects in your anus against your will *but was not successful*? 12. When you had been very *high, intoxicated, or passed out from drugs,* has anyone ever *attempted* to have oral, vaginal, or anal sex with you or tried to put fingers or objects in your anus against your will but was not successful?	10. Has anyone ever *attempted* to have vaginal, oral, or anal sex with you when you did not want to or put fingers or objects in your vagina or anus against your will *but was not successful*? 11. When you had been very *high, drunk, or passed out from alcohol,* has anyone ever *attempted* to have vaginal, oral, or anal sex with you or tried to put fingers or objects in your vagina or anus against your will *but was not successful*? 12. When you had been very *high, intoxicated, or passed out from drugs,* has anyone ever *attempted* to have vaginal, oral, or anal sex with you or tried to put fingers or objects in your vagina or anus against your will but was not successful?

*Female items* displayed to participants indicating female sex and female gender. *Male items* displayed to participants indicating male sex and male gender. *Gender-neutral items* displayed to participants who choose not to indicate a sex, chose a gender that is different than their sex, who describe their gender as transgender, or who do not identify as male, female, or transgender.

*Response options at predeparture*: Regardless of how long ago it happened or who made the unwanted sexual advances…

- 0 = No, this has never happened to me
- 1 = Yes, this happened to me before I started college
- 2 = Yes, this happened to me during college
- 3 = Yes, this happened to me before college and during college

*Response options at last month abroad*: Consider your entire trip abroad. Regardless of when it happened during your trip or who made the unwanted sexual advances…

- 0 = No
- 1 = Yes

Also, on the last month abroad survey, all items will be prefaced with “During your study abroad trip…”

*Response options at 3-month post-return*: Consider the past 3 months (i.e., the time since you have been back in the US since your study abroad trip ended). Regardless of when during this time it happened or who made the unwanted sexual advances…

- 0 = No, this has not happened to me
- 1 = Yes, this happened to me since I have returned from study abroad

Also, on the 3-month post-return survey, all items will be prefaced with “During the past 3 months since you have been home from your study abroad trip…”

